## 3. Materials and Equipment

Materials and equipment to be used in this study is briefly described below. Their specific protocols are presented in detail in Section 4.

### 3.1. Biochemical Variables

Blood samples will be collected in EDTA vacutainer tubes and centrifuged at 3000× *g* for 20 min at refrigerated temperatures. Samples will be stored at −80 °C until analysis. Total cholesterol, c-HDL, c-LDL, triglycerides, glycosylated hemoglobin, and glucose levels will be measured using standard colorimetric procedures, following the manufacturer’s instructions (Spinreact, Girona, Spain), and analyzed with a Mindray BS200 biochemical autoanalyzer (MINDRAY, Shenzhen, China). Plasma concentrations of IL-6 and TNF-α will be assessed using Quantikine immunoassay kits (R&D Systems, Minneapolis, MN, USA).

### 3.2. Body Composition

Body composition will be assessed using a combination of techniques. Bone mineral density and total skeletal muscle mass will be measured with dual-energy X-ray absorptiometry (DXA) (GE Healthcare, Madison, WI, USA). Total body water, intracellular, and extracellular water, as well as phase angle, will be evaluated using bioelectrical impedance analysis (BIA) SECA mBCA 525 (SECA, Hamburg, Germany). Additionally, body fat mass will be measured using air displacement plethysmography (BodPod, COSMED, Rome, Italy).

### 3.3. Epigenetic Variables

For the epigenetic analysis, circulating microRNAs will be isolated from venous blood samples using the mirVana™ miRNA Isolation Kit (Thermo Fisher Scientific, Waltham, MA, USA). Fourteen microRNAs related to inflammation, adipogenesis, and fatty acid metabolism will be analyzed. Specific amplification of each microRNA will be performed using the QuantStudio 3 system (Thermo Fisher Scientific, Waltham, MA, USA), and expression levels will be quantified using the ∆∆Ct method with TaqMan MicroRNA Assays (Thermo Fisher Scientific, Waltham, MA, USA). Additionally, genotyping of polymorphisms related to obesity and lipid metabolism will be performed using TaqMan probes with a StepOnePlus thermocycler (Thermo Fisher Scientific, Waltham, MA, USA).

### 3.4. Metabolic Flexibility

To measure metabolic variables, participants will undergo submaximal exercise tests on a cycle ergometer (Monark Exercise AB, Vansbro, Sweden) or a treadmill (Quinton TM55, WA, USA). Gas exchange during exercise will be measured using a TrueOne 2400 metabolic measurement system (ParvoMedics, Sandy, UT, USA), which will be calibrated before each test. This equipment will allow for the calculation of oxygen consumption (VO_2_), carbon dioxide production (VCO_2_), and the rates of fat and carbohydrate oxidation during exercise.

## 4. Detailed Procedure

### 4.1. Sample Size Calculation

To carry out the present study, 156 young sedentary adults with overweight/obesity will be recruited through a snowball sampling. Considering the body composition changes as the primary outcome, the minimum sample size calculated for the present protocol was 44 participants to reliably detect an effect size of δ ≥ 0.5, assuming a two-sided criterion for detection that allows a maximum Type I error rate of α = 0.05 with a probability of 0.9, and considering a 20% dropout of participants, the sample size has been fixed to 52 participants per group. The statistical software used to determine the sample size was G*Power (v3.1.9.7, Universität Kiel, Düsseldorf, Germany) [15]. 

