It should be noticed that 8 to 20 weeks of FatMax training seem to not alter free fat mass or muscle mass in this population [7,9]. Therefore, combining FatMax training with resistance exercises may increase the lean mass of subjects with obesity, preventing sarcopenic obesity and cardiometabolic disorders related to low muscle mass over the long term [9,10]. On the other hand, it has been demonstrated that fat oxidation during exercise is determined by age, sex, body fat levels, genotype, and the type of exercise in individuals with obesity [11,12]. However, the influence of these moderators on the cardio-metabolic adaptations stimulated by FatMax training remains understudied. In addition, there is scarce information about the molecular mechanisms that become activated by FatMax training to induce positive adaptations in metabolic function and overall fitness. To be precise, Bogdanis et al. [13] and Tan et al. [14] reported that skeletal muscle mitochondrial respiratory capacity and the activity of lipoprotein lipase increased significantly after 10 weeks of FatMax training in overweight and obese individuals. Nevertheless, the impact of FatMax training on epigenetic biomarkers related to mitochondrial biogenesis and the regulation of fatty acid metabolism, such as microRNAs, remains unexplored. In this context, microRNAs such as miR-1, which regulates the expression of CPT1, a key enzyme in the transport of fatty acids to the mitochondria, and miR-145, miR-20a-5p, and miR-29a, which modulate the activity of CD36, a protein involved in the uptake of long-chain fatty acids, have been linked to the development of obesity due to their role in lipid metabolism regulation. However, exploring how these microRNAs can be modified by physical exercise interventions, such as those performed at the intensity of maximal fat oxidation (FatMax), is essential to better understand the underlying molecular mechanisms that could optimize both the prevention and treatment of obesity, thereby enhancing intervention strategies to promote overall well-being [11].

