We hypothesize that FatMax training, with or without resistance exercises, will significantly improve body composition (reduce body fat and increase muscle mass) and metabolic flexibility, increase fat oxidation, and alter epigenetic markers related to adipogenesis and inflammation in overweight and obese young adults. Looking to examine which biological and lifestyle factors moderate the adaptations to FatMax training, we will investigate the influence of age, sex, body fat levels, genotype, diet, psychological variables, and the type of exercise.

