### 2.4. Dependent Variables

The dependent variables include body composition (fat mass and muscle mass), biochemical parameters (glucose, cholesterol), metabolic markers (fat and carbohydrate oxidation rates), and epigenetic markers (microRNAs associated with adipogenesis and fat metabolism).

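### One test's error rate and power are attached to a primary outcome of two variables, fat mass and muscle mass, with no rule for what counts as success

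*Protocol article*

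**What the plan says.** Section 4.1 sets the sample size "Considering the body composition changes as the primary outcome". It assumes "a two-sided criterion for detection that allows a maximum Type I error rate of α = 0.05", power of 0.9 and a standardised effect of at least 0.5. This gives a minimum of 44, raised to 52 per group for 20% dropout.

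Section 2.4 shows what the outcome contains: "The dependent variables include body composition (fat mass and muscle mass". Section 3.2 begins "Body composition will be assessed using a combination of techniques" and gives each component its own device. Muscle mass comes from DXA ("Bone mineral density and total skeletal muscle mass will be measured with dual-energy X-ray absorptiometry (DXA") and fat mass from air displacement plethysmography. Bioimpedance supplies body water and phase angle. Section 4.5.2 repeats this allocation.

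Section 4.5.5 tests each variable, with a significance threshold of p < 0.05 throughout. The Tukey, Dunn and Bonferroni procedures it names belong to the comparison of treatments. Nothing adjusts for or ranks the body composition variables.

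The Introduction predicts that FatMax training, with or without resistance work, will "significantly improve body composition (reduce body fat and increase muscle mass". It also reports that "8 to 20 weeks of FatMax training seem to not alter free fat mass or muscle mass" in this population.

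**The concern.** An error rate and a power describe a test, or a stated rule for combining tests. Section 4.1 gives one of each for an outcome that section 2.4 splits in two, and no section says how the two results combine into a verdict on the primary outcome.

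Without that rule, the primary claim could rest on whichever variable reaches p < 0.05, and the 5% limit would not hold. If both results are needed, the limit holds but the power does not. In either case the effect size of 0.5 is tied to no named variable, so a reader of the results cannot tell which comparison the trial was designed to decide.

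**Working it through.** **Inputs.** From 4.1: two-sided alpha 0.05, power 0.9, effect size 0.5, minimum 44. From 2.4: two variables. From 4.5.5: each variable tested at 0.05. The correlation between the two tests is not given, so I assume a range of 0 to 0.9.

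**Step 1: reproduce the 44.** For one paired t-test the approximate formula is n = ((z for alpha + z for power) / d)² + (z for alpha)² / 2.
- ((1.960 + 1.282) / 0.5)² = 42.03
- 1.960² / 2 = 1.92
- Sum: 43.95. The exact noncentral t calculation gives 43.995, rounded up to 44.

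The stated figure is therefore one paired test, within one group, on one variable, at the full 0.05.

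**Step 2: either variable suffices.** The chance of at least one false positive is 1 − P(both test statistics lie within ±1.96). With independence this is 1 − 0.95² = 0.0975. From the bivariate normal distribution:

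| Correlation | Type I error |
|---|---|
| 0 | 9.75% |
| 0.3 | 9.5% |
| 0.5 | 9.1% |
| 0.7 | 8.4% |
| 0.8 | 7.8% |
| 0.9 | 7.0% |

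A simulation of the three-arm ANOVA (44 per arm, 20,000 runs, no true effect) agrees: 9.7% at correlation 0 and 7.9% at 0.8.

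**Step 3: both variables required.** The type I error stays at or below 5%. If each test has power 0.9, joint power is 0.9 × 0.9 = 0.81 when they are independent. Whatever the dependence, it lies between 0.9 + 0.9 − 1 = 0.80 and 0.90. It reaches the stated 0.9 only if the two tests always succeed or fail together.

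**Step 4: ways to restore 5%.**
- One named primary variable, with the second tested only after success on the first: 5%, with no alpha lost on the first.
- 0.025 for each variable: at most 5%. The protocol's own paired calculation then needs 53 instead of 44 (52.2 rounded up), and power at 44 falls from 90% to 84%.

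**Step 5: the comparison of interest.** Section 4.2 compares groups A and B with group C. Taking 0.5 as the standardised difference in change between two arms, an unadjusted two-sided test at 0.05 has 64% power with 44 per arm, and needs about 86 per arm for 90%.

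**The case against.** The strongest objection is that no section says that success on one variable is enough. The Introduction joins the two with an and. If both are required, testing each at 0.05 causes no inflation. This stands, and it rules out a reading that a reader might infer, namely that the trial's true type I error simply is 8% to 10%. That figure is conditional on an unstated rule. The objection does not rescue section 4.1, however, because under the both-required rule the stated power fails instead (step 3).

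A second objection is that a condensed article may leave multiplicity detail to a fuller document. That is fair for the detail. But the article itself fixes the primary outcome, the error limit, the power, the per-variable testing and the threshold, and these do not fit together.

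Three further readings are tempting and not supported:

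- **Three devices, hence three or more primary tests.** Three independent tests would give 1 − 0.95³ = 14.3%. But fat mass and muscle mass each have one device, and section 2.4 names no third component. The firm count is two.
- **Counting within-arm pre/post tests.** Six independent tests (two variables, three arms) would give 1 − 0.95⁶ = 26.5%. This includes changes within the placebo arm, which would not support a treatment claim.
- **The effect size cannot apply to muscle mass with FatMax alone.** The Introduction's statement on muscle mass is hedged, and 0.5 is given as an effect to detect, not as a forecast for every variable in every arm. What remains is a tension between that statement and the hypothesis. It is worth resolving, but it has no bearing on type I error.

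**Conclusion.** The point holds in a conditional form. Section 4.1 gives one test's error rate and power to a two-variable outcome without a decision rule. If either variable suffices, the type I error is about 7% to 10% against a stated maximum of 5%. If both are required, power is about 81% under independence against a stated 90%. The first range rests on the assumed correlations of 0 to 0.9. The second figure assumes 90% power for each variable. Which of the two applies cannot be determined from the protocol.

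The inconsistency should be corrected before any outcome data are examined, because the choice of primary variable loses its protective value afterwards.

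**What to change.** In section 4.1:

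1. Name one primary variable, time point and comparison. An example is the between-arm difference in change in body fat mass, by air displacement plethysmography, from baseline to week 16.
2. Test DXA muscle mass second, at 0.05, only if the first test is significant. Label the remaining body composition measures secondary.
3. Restate the power for the between-arm comparison actually planned, including the adjustment across arms.
4. Reconcile the Introduction's prediction of muscle gain from FatMax alone with its own statement that such training seems not to change muscle mass.

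**Cost.** Items 1, 2 and 4 change wording only and add no participants. The price of the sequence is that muscle mass alone can no longer carry the primary claim. The protocol does not rank the two variables, and lean mass is its rationale for adding resistance work, so the investigators may prefer 0.025 for each. That is equally valid, with the loss of power shown in step 4. Item 3 is more than wording: at the current size the honest power may be well below 0.9, and the investigators must then either accept this openly or revisit the sample size.

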### 4.2. Randomization and Blinding

The protocol involves the assignment of 52 subjects to one of three groups. Group A will comprise participants performing low-intensity training sessions within their FatMax zone. Group B will comprise participants who will perform both FatMax zone exercises as well as muscular resistance exercises (MRE). Both groups will be compared to group C, where participants will maintain their physical activity following an isoenergetic diet, evaluated through 24 h dietary records every four weeks.

For groups A and B, subjects will be allowed to perform their FatMax training on a treadmill or stationary bicycle, whichever is of their preference. The random sequence for participant assignment will be coded with SPSS 22 Software, looking for an equal distribution of both genders, BMI (overweight (≥25 and <30 kg/m^2^) and obesity grade 1 (≥30 and <35 kg/m^2^). All the evaluations and training sessions will be conducted in the Conahcyt National Laboratory of Body Composition and Energetic Metabolism (LaNCoCoME). The general process is shown in Figure 1.

To ensure single blinding, a researcher external to this study will enter data into the software on separate datasheets so that these researchers can analyze them without having access to treatment assignment information, storing all participant files in numerical order in a secure and accessible location. All files will be retained for a period of five years.

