#### 4.5.5. Data Analysis

The normality and homoscedasticity of the variables will be assessed using the Kolmogorov–Smirnov and Levene tests for each group. A student’s *t*-test will be used to analyze the differences between the pre- and post-treatment values for each variable if the data follows a normal distribution. If the data are non-parametric, the Mann–Whitney U test will be used. Statistical analysis between treatments will be conducted using ANOVA with Tukey’s post-hoc test in the case of parametric distribution and/or Kruskal–Wallis H and Dunn’s Post-hoc test for non-parametric distribution, with a Bonferroni setting for comparing intervention-induced changes. Additionally, Pearson and/or Spearman correlation tests will be used to establish associations between variables. Multivariate linear regression models will also be constructed to explore the contribution of treatment on main outcomes, which will be adjusted by potential confounder factors including age, sex, dietary variables, psychological variables, and baseline measurements. Moreover, multiple imputations will be used for generating replacement values for missing data. Statistical significance will be considered at *p* < 0.05, and all statistical analyses will be conducted using IBM SPSS package version 22 (SPSS Inc., IBM Company, Chicago, IL, USA) and GraphPad Prism v8.1 (GraphPad Software, La Jolla, CA, USA).

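### The 44 per group matches a paired pre-post test within one group; for the between-group comparisons, power at δ = 0.5 is about 61–64% (43–49% after correction), not 90%

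*Protocol article*

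**What the plan says.** Section 4.1 (Sample Size Calculation) sets the outcome with "Considering the body composition changes as the primary outcome" and states that "the minimum sample size calculated for the present protocol was 44 participants to reliably detect an effect size of δ ≥ 0.5". The error rate is given by "assuming a two-sided criterion for detection that allows a maximum Type I error rate of α = 0.05" and the power by "with a probability of 0.9". The figure is then carried to the group level: "considering a 20% dropout of participants, the sample size has been fixed to 52 participants per group". G*Power is named as the software. The section does not give the test, the SD to which δ refers, or a pre-post correlation.

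Section 4.2 (Randomization and Blinding) states the comparison the trial is randomised for. After describing the two training groups it says "Both groups will be compared to group C".

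Section 4.5.5 (Data Analysis) plans several analyses:
- t-tests of pre against post values;
- for the comparison of groups, "Statistical analysis between treatments will be conducted using ANOVA" with Tukey's post-hoc test, or Kruskal–Wallis with Dunn's test, and a Bonferroni setting for the changes under intervention;
- regression models of the treatment contribution, adjusted for baseline and other covariates.

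**The concern.** For a standardised difference of 0.5 with two-sided α = 0.05 and 90% power, a comparison of two independent groups needs a sample in the eighties per group. A figure of 44 is about half that, which suggests a one-sample or paired calculation. Such a test asks whether one group changed from its own baseline. It uses neither group C nor the randomisation.

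If so, the 90% belongs to a secondary kind of evidence, and the controlled comparison has much lower power than a reader of section 4.1 would assume. A non-significant A-versus-C, B-versus-C or A-versus-B result could then be taken as good evidence of no effect, when the trial had only a modest chance of detecting the effect it names.

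**Working it through.** **Inputs (section 4.1).** δ = 0.5, two-sided α = 0.05, power 0.90, minimum n = 44, dropout 20%, 52 per group. Sections 4.2 and 4.5.5 give three groups, compared by ANOVA with post-hoc correction. All results use the exact noncentral t (noncentral F for the overall ANOVA test).

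**Step 1: reproduce 44.** For a paired test, the noncentrality is δ√n on n − 1 degrees of freedom.
- n = 44: 0.5 × √44 = 3.317, critical value 2.017, power 0.9000.
- n = 43: power 0.8931.

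So 44 is exactly the smallest n. Other standard forms do not return 44 from these inputs:

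| Test | n for 90% power |
|---|---|
| Paired, two-sided | 44 |
| Paired, one-sided | 36 |
| Two independent groups, two-sided | 86 per group |
| Two independent groups, one-sided | 70 per group |
| Three-group ANOVA, assumed f = 0.25 | 207 in total |
| Group-by-time interaction, three groups, assumed f = 0.25 and r = 0.5 | 54 in total |
| Group-by-time interaction, two groups, same assumptions | 46 in total |

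The last row is close, but it is a total over two groups, whereas section 4.1 carries 44 forward to a number per group.

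**Step 2: sample needed between groups.** The noncentrality is δ√(n/2) on 2n − 2 degrees of freedom. For δ = 0.5 and 90% power, n = 86 per group at α = 0.05, and n = 110 per group at α = 0.05/3 (Bonferroni over three pairs).

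**Step 3: power the design has at δ = 0.5.** After the stated dropout, 52 × 0.8 = 41.6, so about 41 per group would be analysed. As an example, at n = 44 the noncentrality is 0.5 × √22 = 2.345 and the critical value 1.988, which gives 0.640. Tukey uses the pooled error on 3n − 3 degrees of freedom.

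| Analysed per group | Unadjusted | Bonferroni, 2 comparisons with C | Bonferroni, 3 pairs | Tukey, 3 pairs |
|---|---|---|---|---|
| 41 | 60.9% | 49.5% | 43.2% | 45.9% |
| 44 | 64.0% | 52.8% | 46.5% | 49.2% |
| 52 (no dropout) | 71.4% | 60.9% | 54.8% | 57.3% |

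The overall ANOVA test with 3 × 44 = 132 analysed depends on the pattern of means:
- Means of 0, 0.25 and 0.5 SD (f = 0.204) give 53.5%.
- Means of 0, 0.5 and 0.5 SD (f = 0.236) give 66.6%.

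**Step 4: difference detectable with 90% power.** At 44 per group it is 0.699 SD unadjusted and 0.797 SD with Bonferroni over three pairs. At 41 per group it is 0.725 SD and 0.827 SD.

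**Scale.** Steps 2 to 4 take δ in SD units of the variable compared, that is, the change. This is the scale the paired calculation implies.

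**The case against.** Four points can be made for the plan.

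- **The test is inferred.** Section 4.1 names none, and an article may leave the G*Power test family to the full protocol. This is true, but the exact match is strong evidence. The conclusion also survives without it: 44 per group does not give 90% power for a two-group difference of 0.5 SD, whatever produced the 44.
- **A pre-post t-test is a planned analysis.** The number does fit something in section 4.5.5. The fault is therefore that the powered analysis is not the randomised comparison, rather than a slip in the arithmetic of the paired formula.
- **Baseline adjustment could recover the power.** This is the strongest point, because section 4.5.5 also plans regression adjusted for baseline. If δ were in SD units of the raw measurement, two-group power at 44 per group, unadjusted for multiplicity, would depend on the pre-post correlation r: 68% at r = 0.3, 76% at 0.5, 90% at 0.7 and 97% at 0.8. With Bonferroni over three pairs these become 51%, 61%, 80% and 93%. A high enough correlation would thus support the claim. But no correlation or raw-SD scale is stated, the outcome is described as changes, the group comparison is an ANOVA, and the regression is presented as exploratory.
- **The correction may cover fewer comparisons.** The scope of the Bonferroni setting is not stated. If it covers only the two comparisons with C, power is 49.5–52.8%, slightly above the three-pair range and still far from 90%.

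What stands is that the size of the shortfall depends on the SD scale and on the scope of the correction.

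**Conclusion.** The concern holds. With δ in SD units of change, the stated 90% describes a within-group test, and the between-group comparisons do not have it. Power for 0.5 SD is about 61–64% at 41–44 analysed per group, and 43–49% with Bonferroni or Tukey over three pairs. Even with all 52 per group analysed and no correction it is 71%. A true difference of 0.5 SD would therefore be missed about 36–39% of the time without correction and 51–57% with it. At 90% power the trial can detect about 0.70–0.72 SD, or 0.80–0.83 SD after Bonferroni, rather than 0.5.

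That 44 came from a paired test is an inference from an exact match. The percentages rest on the change-SD scale. A raw-SD scale combined with baseline adjustment and a correlation of about 0.7 would restore 90% before correction, but the document states neither that scale nor any correlation.

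**What to change.** Keep 156 participants and rewrite section 4.1 so that it:

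1. Says that 44 is a paired, within-group calculation (δ = 0.5 SD of change, two-sided α = 0.05, power 0.90).
2. Gives the between-group position, for example: with 41–44 analysed per group, there is 90% power for a between-group difference of about 0.70–0.72 SD of change (0.80–0.83 SD with Bonferroni over three pairs). For 0.5 SD, power is about 61–64% unadjusted, 43–47% with Bonferroni and 46–49% with Tukey.
3. Names the one body-composition variable and the SD to which δ refers, for example the change in BodPod fat mass at week 16.
4. States how many comparisons the correction covers. If it is only the two with group C, the corrected power is about 49–53%.

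If the sponsor did intend a baseline-adjusted comparison on the raw-SD scale, section 4.1 should say so and give the assumed correlation with its source.

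The cost is wording only: no added participants and no change to the design. The stated power becomes less favourable. Keeping 90% for 0.5 SD of change would instead need 86 per group, or 86/0.8 = 107.5, so 108, with 20% dropout. With Bonferroni over three pairs it would need 110 per group, or 110/0.8 = 137.5, so 138.

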### 2.2. Participants Eligibility Criteria

The study will recruit 156 sedentary young adults aged between 18 and 35 years, all of whom will have a body mass index (BMI) ≥ 25 kg/m^2^. Participants will be recruited through snowball sampling. The participants will be eligible to participate in this study if they meet the eligibility criteria detailed in Table 1.

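### The 20% dropout allowance is miscalculated: 52 per group retains the stated minimum of 44 only up to 15.4% loss, and at 20% dropout 41–42 remain

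*Protocol article*

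**What the plan says.** The sample-size paragraph is in Section 4.1 of the protocol article. It says that "the minimum sample size calculated for the present protocol was 44 participants". The inputs listed for that number are a standardised effect of at least 0.5, a two-sided significance level of 5% and a figure of 0.9, the last of which I read as the power. The paragraph names G*Power as the software but no statistical test. The move from the minimum to the recruited number is made in these words: "considering a 20% dropout of participants, the sample size has been fixed to 52 participants per group".

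The other sections use the same figures. Section 2.2 says "The study will recruit 156 sedentary young adults", and Section 4.2 says "The protocol involves the assignment of 52 subjects to one of three groups". Since 3 × 52 = 156, the totals agree. No other dropout rate and no other base sample size appears in the document.

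**The concern.** A dropout allowance should leave the required number once the assumed fraction has been lost. The required number is therefore divided by one minus the dropout rate. Multiplying by one plus the rate gives too few, because the loss applies to everyone recruited and not only to the minimum. The step from 44 to 52 looks like the second calculation.

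At stake is whether the stated 90% power holds under the plan's own 20% dropout assumption. The paragraph is the only basis given for recruiting 156.

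**Working it through.** **Inputs, all from Section 4.1.** Base size 44; standardised effect 0.5; two-sided α = 0.05; power 0.90; dropout 20%; 52 per group. The 44 is read as a per-group figure because the text takes it straight to a per-group 52.

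**Step 1: reproduce the 44.** For a paired (one-sample) t-test with standardised change d, power comes from the noncentral t distribution with n − 1 degrees of freedom and noncentrality d√n. Solving for 90% power at d = 0.5 and two-sided α = 0.05 gives n = 43.995, which rounds up to 44. Other designs at the same effect size, α and power do not give 44:

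| Calculation | Required n |
|---|---|
| Paired t-test, two-sided | 44 |
| Paired t-test, one-sided | 36 |
| Two-sample t-test, two-sided | 86 per group |
| Two-sample t-test, one-sided | 70 per group |
| Three-group ANOVA, f = 0.25 | about 206 in total |
| Three-group ANOVA, f = 0.5 | about 54 in total |

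That the 44 rests on a within-group paired test is therefore an inference from the arithmetic. The document does not say it.

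**Step 2: reproduce the 52.**
- Division: 44 / (1 − 0.20) = 55. This is not 52.
- Multiplication: 44 × 1.20 = 52.8. This gives 52 if truncated and 53 if rounded up.

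Only the truncated product matches the plan.

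**Step 3: what 52 per group delivers.**
- Remaining after 20% dropout: 52 × 0.80 = 41.6, so 41 or 42.
- Largest loss that still leaves 44: 1 − 44/52 = 8/52 = 15.4%.
- Size needed at 20% dropout: 55 per group, since 55 × 0.80 = 44. The total is 3 × 55 = 165.
- Shortfall: 55 − 52 = 3 per group; 165 − 156 = 9 in total.

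**Step 4: power on the paired test that reproduces 44 (d = 0.5, two-sided α = 0.05).**

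| n analysed per group | Noncentrality 0.5√n | Power |
|---|---|---|
| 44 | 3.317 | 0.900 |
| 42 | 3.240 | 0.886 |
| 41 | 3.202 | 0.878 |

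The loss is 90.0 − 88.6 = 1.4 to 90.0 − 87.8 = 2.2 percentage points. Expressed as an effect, 90% power is kept at about 0.5 × √(44/42) = 0.51 to 0.5 × √(44/41) = 0.52 instead of 0.50.

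**The case against.** The strongest reply is that the slip hardly matters. It costs about two points of power at most, and only if dropout goes beyond 15.4%. Section 2.7 describes active retention measures that may keep dropout below that level. This stands as a statement about size, and it is why the point should not be pressed harder. It does not rescue the figure: the 20% is the plan's own assumption, and 52 does not cover it. Rounding does not explain it either, since even 44 × 1.2 rounds up to 53.

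The planned multiple imputation (Section 4.5.5) is no answer to the arithmetic. Section 4.1 itself treats dropout as a loss to be made good by recruitment. Section 4.5.4 restricts the data to participants who complete at least 80% of sessions and measurements.

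Two stronger readings are tempting, and the document supports neither.

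- A reader might infer that the attendance exclusions (below 75% in Section 2.7 and Figure 1, below 80% in Section 4.5.4 and Table 1) come on top of the 20% with nothing allowed for them. Section 4.1 does not define dropout, and Table 1 lists low attendance among its exclusion/elimination criteria, so the 20% may already include these participants. Adding a further loss would need a rate that the document does not give, and might count the same people twice.
- A reader might infer that the dropout error leaves the comparisons between groups badly underpowered. On a two-sample test with a standardised difference of 0.5, power is 0.64 at 44 per group and 0.61 at 41. Nearly all of the distance from 0.90 is there before anyone drops out. It comes from the choice of test behind the 44, which is a separate question.

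**Conclusion.** The concern holds in a limited form. The 52 per group is wrong as a 20% dropout allowance on 44: it covers 15.4% loss, and 55 per group would be needed. Under the plan's own assumption 41–42 per group remain, and power is about 88–89% instead of the stated 90%.

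The headcount rests only on figures in Section 4.1 and on reading 44 as per group. The power figures also rest on the inference that 44 came from a paired t-test. That the minimum of 44 is missed is conditional: it follows if the full 20% is lost, not if loss stays at or below 15.4%. The document does not show how many participants the attendance rules will remove, or whether the 20% already counts them.

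**What to change.** Restate the last step of Section 4.1 along these lines: *52 per group retains 44 with up to 15% loss; at 20% dropout 41–42 per group remain, with power of about 0.88 for the test on which 44 was based.* In the same paragraph, name that test, and state whether the 20% includes participants removed for low attendance.

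The cost is a change of wording and a slightly less favourable power figure. No added recruitment is needed. For information, keeping 44 per group at 20% dropout would take 55 per group, which is 9 more participants in total.
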